### **11.3 Exploratory Objective: To estimate the VE against SARS-CoV-2 viral load as a proxy of transmission**

Endpoint: Peak viral load (and subgenomic RNA, if tested), as a proxy for transmission, in RT-PCR positive swabs

Data sets: PP-ITT, PP-PAS, PP-PAS2

Approach: Linear regression summaries of the peak viral load on the log10 scale will be used with vaccination status (no vaccine, 1 dose, 2 doses) as the covariate of interest, adjusted for age and sex.

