## 6.5 Final Study Visit

The final ancillary study swab will be collected by December 17, 2021 at which point the participant's ancillary study participation will be completed (Appendix).

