| 
 
To determine the sequence of breakthrough SARS-CoV-2 infections*
 
                                                                                                                      | 
 
Viral genome sequence of RT-PCR-positive samples
 
                                                                                                                                                                                                                                                                                                                                                                                                                 |
| 
 
To estimate the VE on duration of infection
 
                                                                                                                                           | 
 
Duration of shedding as indicated by RT-PCR in vaccinated vs placebo recipients
 
                                                                                                                                                                                                                                                                                                                                                                                  |
| 
 
To estimate the VE against SARS-CoV-2 viral load as a proxy of transmission
 
                                                                                                           | 
 
Reduction in viral load (and perhaps subgenomic RNA), as a proxy for transmission, in RT-PCR-positive samples from vaccinated vs placebo recipients
 
                                                                                                                                                                                                                                                                                                              |

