### 3. GENERAL DATA ANALYSIS CONSIDERATIONS

#### 3.1 Analysis Set(s)

For analysis purposes, the following populations are defined:

**Intention to Treat (ITT):** All enrolled participants who had at least one valid result in the lab results dataset

**Modified Intention to Treat (mITT):** All ITT participants who were not identified as having SARS-CoV-2 infection, either through RT-PCR or serological testing, prior to administration of the second dose of the first dosing series.

**Primary analysis set (PAS):** The intention of the SNIFF protocol was to enroll participants at their second dose of the first vaccination series and immediately start swabbing. This would allow exclusion of all participants who were previously infected. However, many participants enrolled after the second dose of the initial series, and it may be impossible to determine if they acquired infection in between that second dose and the first swab. We define this data set to account for this by limiting inclusion to mITT participants enrolled before 4 weeks post second dose of the initial series. Primary analyses will be conducted on this data set.

**Primary analyses set 2 (PAS2):** All mITT participants enrolled by July 12, 2021. Primary analyses will be conducted on this data set. This analysis set serves as a complement to PAS in case too many participants have enrolled after 4 weeks post second dose of the primary series. 82.4% were enrolled by this date.

**Post crossover analysis set (PCAS):** All mITT participants enrolled before 4 weeks post second dose of the crossover series without evidence of prior infection before or at the second dose of the crossover series.

**PCR-positive (PP-ITT):** All participants in the ITT population with SARS-CoV-2 RNA detected by RNA-RT-PCR as part of the SNIFF study (as determined by the lab).

**PCR-positive PAS (PP-PAS):** All participants in the PAS with SARS-CoV-2 RNA detected by RNA-RT-PCR as part of the SNIFF study (as determined by the lab).

**PCR-positive PAS (PP-PAS2):** All participants in the PAS2 with SARS-CoV-2 RNA detected by RNA-RT-PCR as part of the SNIFF study (as determined by the lab).

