### Change of predominant variant in the United States during follow-up time

From the first enrollment in this study to the end of follow-up, the predominant SARS-Cov-2 strain changed from alpha to delta (Figure 2). We will plan to repeat analyses in the subset of sites in states where delta was the most prevalent strain (>80%) at the start of enrollment (according to nextstrain.org).

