### **11.5 Exploratory Objective: To explore whether observed VE against COVID-19 illness reflects a transition from symptomatic into asymptomatic infections versus an absolute reduction in all SARS-CoV-2 infections**

Endpoint: Ratio of asymptomatic to symptomatic infections in vaccinated vs unvaccinated (defined as pre-second dose) recipients. Data on symptomatology will be extracted from the Phase 3 trial database, which will be separate but linkable to the ancillary study.

Approach: This objective will be met as a composite of previous analyses and will be addressed in a synthesizing discussion of overall results. Post hoc analyses may be added to aid in understanding of results.

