## **12. ADDITIONAL PLANNED ANALYSES**

In this section, we list planned supporting analyses at a high level. Details for these analyses will be guided from the results reported based on the analyses in this document.

- Repeat analyses in calendar time instead of study time.

- Infection endpoint expanded to include serological testing from the parent study.
- Estimating the association between time since vaccination and characteristics of viral kinetics.
- Modeling of viral load curves to estimate duration of shedding in days as well as peak viral loads. Models are in development that extend those presented in Stankiewicz Karta et al (2021).
- Multistate models to estimate the disease course, reflecting transitions from uninfected to asymptomatic infection (definition may vary), to symptomatic infection to recovery. This would be similar to an illness-death model.
- Models that treat vaccination status as a time-varying covariate. These models will also need to include information on background distribution of variants over time and geography.
- Models that compare total potential infectious time averted due to vaccination.

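### SAP 11.3 compares peak viral load by vaccination status with no crossover cut-off and no calendar or variant term, so status is tied to calendar time

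*Supplement*

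**What the plan says.** The viral-load analysis in SAP v2.0 section 11.3 has "vaccination status (no vaccine, 1 dose, 2 doses) as the covariate of interest, adjusted for age and sex". Its line on analysis sets reads "Data sets: PP-ITT, PP-PAS, PP-PAS2". Section 3.1 defines the first of these as "All participants in the ITT population with SARS-CoV-2 RNA detected by RNA-RT-PCR as part of the SNIFF study", and the other two in the same way within the PAS and PAS2. None has an end date or a crossover cut-off.

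Four other places bear on this:

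- **Duration.** Protocol v4.0 section 6.5 says "The final ancillary study swab will be collected by December 17, 2021". Section 2.1 dates the start of the blinded crossover to 10 August 2021, so swabbing continued well past it.
- **Variant.** SAP 3.2 says that during follow-up "the predominant SARS-Cov-2 strain changed from alpha to delta". It goes on to accept that the durability estimates will be confounded by variant. Protocol 3.1 says that crossover coincided with the emergence of delta.
- **Time-varying status.** SAP section 12 lists models that treat vaccination status as time-varying and adds: "These models will also need to include information on background distribution of variants over time and geography".
- **Endpoint.** SAP 2.2 defines this viral-load endpoint "in RT-PCR-positive samples from vaccinated vs placebo recipients". The neighbouring section 11.2, on duration of shedding, uses randomisation arm.

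Section 11.5 has a related contrast: "Ratio of asymptomatic to symptomatic infections in vaccinated vs unvaccinated (defined as pre-second dose) recipients".

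**The concern.** Vaccination status here is not the randomised assignment. It is current status, and crossover makes current status a function of date. A placebo-arm participant stops being unvaccinated at crossover dose 1. Enrolment required two doses of study product, so the one-dose level arises essentially in the delayed arm between the crossover doses. After crossover dose 2, participants in both arms are at two doses.

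If viral load differs between variants, or drifts over calendar time for any other reason, the model assigns part of that difference to the vaccine, because only age and sex are adjusted for. The result is offered as a proxy for transmission, so an effect could be masked or created. The SAP recognises the problem for durability and for time-varying models but does not carry it into 11.3.

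Section 11.5 has the same lack of concurrency. It also classes one-dose infections as unvaccinated.

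**Working it through.** **Inputs.** All counts and person-years (PY) are from Table S2 of the supplement, censored at crossover dose 2 and at crossover dose 1.

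| Set, arm | To dose 2: infections / PY | To dose 1: infections / PY |
|---|---|---|
| mITT vaccine | 16 / 110.3 | 5 / 76.3 |
| mITT placebo | 28 / 50.1 | 13 / 35.3 |
| PAS vaccine | 13 / 87.2 | 5 / 62.6 |
| PAS placebo | 21 / 38.7 | 10 / 28.4 |

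**Step 1: reproduce the reported figures.** Rate = infections / PY × 100, with exact Poisson limits. mITT vaccine: 16/110.3 = 14.5 (8.3, 23.6), against 14.5 (8.3, 23.5) reported. mITT placebo: 28/50.1 = 55.9 (37.1, 80.8), against 55.8 (37.1, 80.7). All eight rows agree to within 0.1, so the counts can be used.

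**Step 2: place infections by status and timing.** The rows are nested, so infections between the crossover doses = (to dose 2) − (to dose 1).

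| Status | mITT | PAS |
|---|---|---|
| No vaccine (placebo arm, before dose 1) | 13 | 10 |
| One dose (placebo arm, between doses) | 28 − 13 = 15 | 21 − 10 = 11 |
| Two doses, before dose 1 | 5 | 5 |
| Two doses, between crossover doses | 16 − 5 = 11 | 13 − 5 = 8 |

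Share of two-dose infections after crossover dose 1: mITT 11/16 = 69%, PAS 8/13 = 62%. The share for no-vaccine infections is essentially zero by construction.

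**Step 3: infections after crossover dose 2.** Their number is not given. All would be two-dose and late, so the shares above are lower bounds. With an assumed 10, 20 or 50 more in the mITT set, the share is 21/26 = 81%, 31/36 = 86% or 61/66 = 92%.

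**Step 4: check on person-time.** Table S3 lists 30,734 expected swab windows in the early arm and 14,518 in the delayed arm. At two windows a week and 52.18 weeks a year, that is 294.5 and 139.1 PY. Two-dose time is 294.5 + (139.1 − 50.1) = 383.5 PY. The part after crossover dose 1 is (294.5 − 76.3) + (139.1 − 50.1) = 307.2 PY, or 80%. The same sum with received windows (19,417 and 9,072) gives 66%. This is approximate, since Tables S2 and S3 count follow-up differently.

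**Step 5: did conditions change?** Vaccine-arm incidence was 6.6 per 100 PY before crossover dose 1. Between the doses it was 11/(110.3 − 76.3) = 11/34.0 = 32.4. The two periods clearly differed; these figures do not say why.

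**Step 6: how large could a variant bias be?** Let d be the delta-minus-alpha difference in mean log10 peak load, L the late share of two-dose infections and p the delta share of early infections, and take all late infections as delta. Then bias = d × L × (1 − p). None of d, L or p for the full set is in the documents. Assumed ranges are d 0.3 to 1.0, L 0.69 to 0.90 and p 0.3 to 0.9:

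- low end: 0.3 × 0.69 × 0.1 = 0.02 log10
- high end: 1.0 × 0.90 × 0.7 = 0.63 log10

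The range runs from negligible to large. A negative d would reverse the sign.

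**The case against.** **Mitigation is planned.** SAP 3.2 foresees repeating analyses in states where delta was predominant. Section 12 lists calendar-time repeats, viral-load-curve models and time-varying vaccination models. Section 11 allows ad hoc support. This stands in part, but none of it is specified for 11.3. The 3.2 subset depends on delta exceeding 80% at the start of enrolment, and section 12 is explicitly high-level.

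**Confounding by variant is not demonstrated.** A reader might infer that the viral-load estimate is in fact biased by the alpha-to-delta change. The documents do not support that. No lineage counts by status are given, and if most no-vaccine infections were already delta, the variant part is small.

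**Late is not a calendar cut.** A reader might also infer that only the 5 mITT two-dose infections before crossover dose 1 are concurrent with the no-vaccine group. But dose 1 is each participant's own date, and delayed vaccination ran through August and September. Some of the 11 infections between doses may coincide with no-vaccine infections in participants not yet crossed over. Anyone who went on swabbing without crossing over would also remain unvaccinated.

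**The arm comparison is not a clean randomised contrast.** Viral load is measured only in infected participants, a group formed after randomisation; SAP 11.2 itself acknowledges post-randomisation selection. Comparing arms restores concurrency and no more. Up to crossover dose 2, 15 of the 28 placebo-arm infections (54%) followed an active dose. Both points stand and shape the fix.

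**Section 11.5 specifies no model.** It is a synthesising discussion, so only a modest addition is warranted there.

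**Conclusion.** The concern holds as a structural one. On the text of 11.3 and 3.1, the status comparison is unrestricted in time and adjusted only for age and sex. No-vaccine infections are essentially confined to the period before crossover dose 1, while at least 62% (PAS) to 69% (mITT) of two-dose infections come after it. Status is therefore tied to calendar time and potentially to variant. The size and direction of any resulting bias cannot be determined from the documents.

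This rests on two things. The first is reading the absence of a cut-off, together with the presence of a one-dose level, as meaning that all infections to the end of swabbing are used. The second is taking the mITT and PAS counts as a guide to PP-ITT, PP-PAS and PP-PAS2, for which Table S2 gives no counts.

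The change should be made, but it concerns one exploratory objective and its use as a transmission proxy. The primary and secondary estimates are untouched.

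**What to change.** In SAP 11.3:

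1. Add calendar period of first detection to the vaccination-status model. State-level predominant-variant period, defined as in supporting analysis 3, is an alternative.
2. Report alongside it a concurrent comparison by randomised arm, in line with SAP 2.2 and 11.2, for infections before crossover dose 1 (mITT 5 vaccine versus 13 placebo) and before crossover dose 2 (16 versus 28). With the second, state that 15 of the 28 placebo-arm infections followed one active dose.
3. Use individual lineage only in a sensitivity analysis. Under 11.1, sequencing is routine at N1 Ct of 32 or below and selective above that, so missing lineage depends on viral load, which is the outcome.
4. State that every one of these contrasts conditions on infection.

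In the 11.5 synthesis, also report the asymptomatic-to-symptomatic ratio for concurrent pre-crossover infections.

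The cost is SAP wording and precision; calendar dates are already held. Unadjusted, the standard error of a difference in mean log10 load is the between-person SD times √(1/5 + 1/13) = 0.53 before dose 1, and times √(1/16 + 1/28) = 0.31 before dose 2. The first comparison will be wide and should be presented as such.

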### **11.4 Exploratory Objective: To estimate the efficacy of SARS-CoV-2 rS/M1 vaccine against a composite outcome of asymptomatic/very mildly symptomatic infection plus pre-symptomatic infection**

Endpoint: Proportion of days that are symptom-free on days that RT-PCR positive swabs are collected

Data sets: mITT, PAS, PAS2

Approach: Poisson model with log offset of number of days with RT-PCR positive swabs and appropriate adjustment for post randomization selection bias as determined in supporting analyses for the primary endpoint.

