#### **5. GENERAL ANALYSIS METHODS**

Descriptive statistics that will be used to summarize continuous variables are as follows: mean and standard deviation, median and interquartile range, quartiles, range, and number of missing data values. For categorical variables, descriptive statistics that will be used include the following: frequencies, relative frequencies, and the number of missing data values. Descriptive analyses summarizing baseline and follow-up data will be stratified by state. Line, scatter, and box plots will be used, as appropriate, for longitudinal data representations. Covariates from regression models will be assessed using Wald tests and corresponding 95% confidence intervals, unless otherwise specified. A two-sided alpha level of 0.05 will be used for all statistical tests, unless otherwise specified.

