##### **6.1.2 Compliance to Swabbing**

Participants are expected to swab on Mondays and Thursdays. Thus the weeks are separated into two collection windows – window 1 (Monday, Tuesday, Wednesday) and window 2 (Thursday, Friday, Saturday, Sunday). Alluvial plots will be used to capture completeness of swabbing. Categories: 0 windows, 1 window, or 2 windows per week, discontinued (exited study). These will be created to describe the population overall and by randomization arm.

The number of expected swabs versus resulted scanned swabs will be tabulated overall and by site and randomization arm.

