Endpoint: SARS-CoV-2 detected by RT-PCR on self-collected SNIFF-provided or Novavax-provided nasal swabs, right-censored at the collection time of the last RT-PCR negative swab at or before the earliest of the second dose of the crossover series (vaccine or placebo), 2 weeks post first crossover dose (applicable for cases where the second dose is missed or late), termination, or receipt of EUA vaccine.

Note: Novavax-provided swabs may either be self-collected at home or collected at study visits.

#### Supporting analysis 2

Because the SNIFF population is a subset of the parent study and was selected post-randomization from the parent study, the primary analysis and supporting analysis 1 will be repeated with adjustment for potential confounders. These will be selected from baseline variables that are univariably (adjusted for state) predictive of risk of acquisition of infection or differ by randomization arm with  $p < 0.10$ . If there are inadequate numbers of participants per state, state may be dropped as an adjustment variable.

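### The exploratory Poisson model in SAP 11.4 sets the variance equal to the mean for a count that is bounded and clustered within participants, so its Wald test and interval do not have controlled size, and the direction of the error is unknown

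*Supplement*

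**What the plan says.** The endpoint in SAP v2.0 section 11.4 is "Proportion of days that are symptom-free on days that RT-PCR positive swabs are collected". The approach is a "Poisson model with log offset of number of days with RT-PCR positive swabs", together with "appropriate adjustment for post randomization selection bias as determined in supporting analyses for the primary endpoint". The analysis sets are given as "Data sets: mITT, PAS, PAS2".

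The adjustment referred to is set out in section 9.2, Supporting analysis 2, where "the primary analysis and supporting analysis 1 will be repeated with adjustment for potential confounders". The confounders are chosen from baseline variables. That changes the model for the mean, not the variance.

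Section 5 gives the default inference: "Covariates from regression models will be assessed using Wald tests and corresponding 95% confidence intervals, unless otherwise specified", and "A two-sided alpha level of 0.05 will be used for all statistical tests, unless otherwise specified". Section 11.4 specifies nothing different. Neither section names a robust variance, a dispersion parameter, a GEE, a random effect or a binomial-type model.

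Repeated days per infection arise from the schedule in section 6.1.2: "Participants are expected to swab on Mondays and Thursdays".

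**The concern.** The participant is the unit of randomisation, while 11.4 counts swab days, of which one infection can supply several. Two features of that count conflict with a Poisson variance.

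- **Bound.** Symptom-free days cannot exceed positive days. If days were independent the count would be binomial, and the Poisson variance would be too large by a factor 1/(1-p). The test would then be conservative and the interval too wide.
- **Clustering.** Days in one infection resemble each other: a wholly asymptomatic infection contributes only symptom-free days, an ill one few. The Poisson variance is then too small, the test rejects too often and the interval is too narrow.

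Fitting one row per participant does not cure this, because the participant's total carries the same variance.

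At stake is the interval for a vaccine effect on symptom-free shedding, which also feeds the synthesis planned in 11.5. A reader could not tell whether that interval is too wide or too narrow.

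**Working it through.** **Target.** Section 11.4 states no sample size, power or error rate of its own. Its only numeric target is the 0.05 level of section 5. If the counts really were Poisson, the simulated size of the planned Wald test is 3.9% to 5.0%, so the method meets its target when its own assumption holds. (The only power figure in the SAP, section 2.5, concerns the primary comparison. It reproduces at 0.790 against the stated 80%, but has no bearing here.)

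**Inputs from the documents.** Supplement Table S2, pre-crossover infections: 13 vaccine and 21 placebo in the primary analysis set; 16 and 28 in the mITT set.

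**Inputs assumed, because the documents do not give them.** Symptom-free proportion p, within-participant correlation rho, and mean positive days per infected participant. The only hint at the last is in the supplemental methods: 62 positive unscanned swabs from 11 participants, or 62/11 = 5.6 each.

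**Formula.** With m_w the size-weighted mean number of positive days,

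true variance / Poisson variance ≈ (1-p) × [1 + (m_w - 1) × rho].

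Let positive days be 1 + Poisson(mean - 1). For mean 5, m_w = (4 + 25)/5 = 5.8. Then:

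- p = 0.5, rho = 0.5: 0.5 × (1 + 4.8 × 0.5) = 1.70. Size ≈ 2 × [1 - Φ(1.96/√1.70)] ≈ 13%.
- p = 0.7, rho = 0.2: 0.3 × (1 + 4.8 × 0.2) = 0.59. Size ≈ 2 × [1 - Φ(1.96/√0.59)] ≈ 1%.

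The ratio equals 1 only at rho = [p/(1-p)]/(m_w - 1). At mean 5 days that is 0.49, 0.21 and 0.09 for p = 0.7, 0.5 and 0.3.

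**Simulation under no arm effect.** 13 vs 21 infected participants, beta-binomial symptom-free days, mean 5 positive days, 40,000 trials per cell. The test is the unadjusted Poisson Wald test with SE of the log rate ratio = √(1/Y1 + 1/Y0), where Y1 and Y0 are the arm totals of symptom-free days. Rejection rate at nominal 5%:

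| p | rho 0 | rho 0.2 | rho 0.5 | rho 0.8 |
|---|---|---|---|---|
| 0.3 | 1.8% | 8.9% | 20.1% | 28.7% |
| 0.5 | 0.6% | 4.5% | 13.2% | 20.7% |
| 0.7 | 0.0% | 1.2% | 5.2% | 10.3% |

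With mean 2 days and p = 0.7 the test stays conservative even at rho 0.99 (at most 2.2%). The mITT counts of 16 and 28 give almost the same picture: at mean 5 and p = 0.5, from 0.5% at rho 0 to 24.8% at rho 0.99.

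Over p 0.4 to 0.7, rho 0.05 to 0.8 and mean 2 to 5.6 days, with 13 vs 21 infections, the rate runs from about 0.1% to 27%. For moderate correlation, rho 0.2 to 0.3, it runs from 0.2% to 11.8%.

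**Same data, participant-level sandwich variance with a t reference.** 3.2% to 5.3% over that last grid, and 2.3% to 5.2% over the wider one that includes rho up to 0.99.

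**The case against.** A reader might infer that the 11.4 test has an inflated false-positive rate. The documents do not support that. Without p, rho or days per infection the error has no known sign, and several plausible settings are near nominal: 5.2% at p 0.7 and rho 0.5, and 4.5% at p 0.5 and rho 0.2, both at mean 5 days. The most alarming rates come from long shedding and strong clustering. The 5.6-day figure is weak support for the former: those swabs were unscanned, came from participants picked out for having unscanned positives, and several swabs need not mean several days. Table S3 also shows that only 63.0% of expected collection windows yielded a swab. This part of the objection stands.

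A Wald test can use a robust standard error, and the SAP does not rule one out. That is fair. But the model as named carries the Poisson variance by default, and nothing in 11.4 or section 5 asks for another.

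The simulation is not exactly the written analysis. It uses infected participants only, omits the covariates, and takes pre-crossover counts although 11.4 states no censoring rule. Restricting to infected participants is unavoidable, since the offset is log(0) for anyone with no positive swab. That is a separate defect of the listed analysis sets, and the variance problem remains once it is mended. Covariates would alter the figures but do not supply a variance for clustered days.

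It may also be said that 11.4 is the only evidence on this question and that a claim hangs on its p-value. Neither follows. Section 11 foresees ad hoc support, section 12 lists multistate models of the disease course, and 11.5 is a discussion with no decision rule. A corrected variance also does not remove the limitation of comparing only people who became infected.

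**Conclusion.** The concern holds in a limited form. As written, the 11.4 variance is mis-specified by about (1-p)[1+(m-1)rho], so the Wald test and interval have no controlled size. Under the null with 13 vs 21 infections, the rejection rate is about 0.1% to 27% over the assumed ranges and nominal only where the bound and the clustering happen to offset. The direction cannot be stated from the documents. The result rests on assumed p, rho and days per infection, on beta-binomial days, and on the default model-based standard error being the one used. It touches one exploratory analysis and the discussion in 11.5; the primary and secondary analyses are unaffected. The point is minor, but worth making because a better method is nearly free.

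**What to change.** In 11.4, state that each infected participant's symptom-free days out of PCR-positive days will be modelled with a log link or a binomial (logistic) model, using a participant-level robust variance with a small-sample (t) correction. A beta-binomial model, or a permutation test of arm across participants, would also serve. Report that interval and p-value in place of the model-based Poisson Wald result.

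The cost is one sentence in the SAP and one software option, with no new data. The downside is small: with about 34 to 44 infections (13 + 21; 16 + 28) the robust test is mildly conservative, at about 3% to 5%, and the interval widens if days are strongly clustered.

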| 
 
To estimate the efficacy of SARS-CoV-2 rS/M1 vaccine against a composite outcome of asymptomatic/very mildly symptomatic infection plus pre-symptomatic infection
 
                     | 
 
Proportion of days that are symptom-free on days that RT-PCR-positive swabs are collected
 
                                                                                                                                                                                                                                                                                                                                                                        |
| 
 
To explore whether observed VE against COVID-19 illness reflects a transition from symptomatic into asymptomatic infections versus an absolute reduction in all SARS-CoV-2 infections
 
 | 
 
Ratio of asymptomatic to symptomatic infections in vaccinated vs placebo recipients. Data on symptomatology will be extracted from the Phase 3 trial database, which will be separate but linkable to the ancillary
 
                                                                                                                                                                                                                                              |

\*This document will provide analytical plans for all but the first exploratory endpoint.

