### **11.2 Exploratory Objective: To estimate the VE on duration of infection**

Endpoint: Duration of shedding as indicated by RT-PCR as measured by the number of RT-PCR positive swabs. If a swab is missing between two RT-PCR positive swabs, it will be treated as if it were RT-PCR positive. If there are missing swabs just before the first or after the last RT-PCR positive swab, the endpoint will be interval censored with the interval being: (number of RT-PCR positive swabs, number of RT-PCR positive swabs + number of missing adjacent swabs).

Data sets: PP-ITT, PP-PAS, PP-PAS2

Approach: A Poisson model will be fit with randomization arm as the predictor of interest. Covariates will be included to account for potential post-randomization selection bias. These will include sex, age, and presence of comorbidities measured at the time point closest to but before infection.

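### SAP v2.0 section 11.4 (exploratory) cannot estimate efficacy against A/VMS plus pre-symptomatic infection: its offset is log(0) for participants without a positive swab, and what remains describes only the infected.

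*Supplement*

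**What the plan says.** The objective in SAP v2.0 section 11.4 is an efficacy objective: "To estimate the efficacy of SARS-CoV-2 rS/M1 vaccine against a composite outcome of asymptomatic/very mildly symptomatic infection plus pre-symptomatic infection".

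The endpoint attached to it is a proportion, both in section 2.2 ("Proportion of days that are symptom-free on days that RT-PCR-positive swabs are collected") and in section 11.4. The protocol v4.0 list of exploratory endpoints (3.3.3) carries the same proportion.

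The model in 11.4 is a "Poisson model with log offset of number of days with RT-PCR positive swabs", with adjustment for post-randomization selection taken over from the supporting analyses of the primary endpoint. The analysis sets are given as "Data sets: mITT, PAS, PAS2".

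These sets do not require a positive study swab. Section 3.1 defines mITT as "All ITT participants who were not identified as having SARS-CoV-2 infection, either through RT-PCR or serological testing" before the second dose of the first series; PAS and PAS2 are subsets of it by enrolment date. By contrast, the shedding-duration analysis in 11.2 is assigned to PCR-positive sets ("Data sets: PP-ITT, PP-PAS, PP-PAS2"), and 11.3 uses the same sets. PP-PAS, for example, is "All participants in the PAS with SARS-CoV-2 RNA detected by RNA-RT-PCR as part of the SNIFF study".

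Section 11.4 gives no rule for participants with zero positive-swab days, states no censoring, and names neither the response variable nor the arm term.

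**The concern.** Two faults lie on top of each other.

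- **Fitting.** A log offset needs a positive number for every row. Most rows in the named sets have zero positive-swab days.
- **Estimand.** Once those rows are gone, the analysis conditions on infection, which occurs after randomization and which the vaccine is meant to prevent. A comparison with no person-time and no count of people at risk cannot show how many asymptomatic or pre-symptomatic infections were averted.

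At stake is the answer to this exploratory objective. Section 11.5, which asks whether the vaccine shifts infections towards the asymptomatic or reduces them outright, is to be answered from the preceding analyses, so a misread ratio from 11.4 could carry over into it.

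**Working it through.** **Inputs.** Section 11.4 states no figure, so the counts come from Table S2, censored at crossover dose 2:

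- PAS: vaccine 466 participants, 13 infections, 87.2 person-years; placebo 216, 21, 38.7.
- mITT: vaccine 628, 16, 110.3; placebo 302, 28, 50.1.

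**Check of the inputs.** Rate = infections / person-years × 100.

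- mITT: 16/110.3 = 14.5 and 28/50.1 = 55.9 (stated 14.5 and 55.8).
- PAS: 13/87.2 = 14.9 and 21/38.7 = 54.3 (stated 14.9 and 54.2).
- 1 − rate ratio: 74.0% (mITT) and 72.5% (PAS), against stated VE of 74.8% and 73.5%.

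The small differences in the rates are rounding of person-years; 1 − rate ratio lies within about 1 percentage point of the stated VE.

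**Step 1: how many offsets are undefined.**

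- PAS: 682 − 34 = 648, or 95.0% (453 vaccine, 195 placebo).
- mITT: 930 − 44 = 886, or 95.3% (612 vaccine, 274 placebo).

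These shares hold up to crossover dose 2. Over full follow-up they would be somewhat lower; if mITT infections doubled (an assumption), (930 − 88)/930 = 90.5%.

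**Step 2: what a fit does with these rows.** In a small test with zero-day rows, a Poisson GLM in statsmodels stopped with an invalid-value error. In one simulated data set with the mITT counts, the infected-only rate ratio was 0.938. Adding the 886 uninfected rows with 0.000001 days in place of zero again gave 0.938. The uninfected carry no information in this model.

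**Step 3: what the model estimates.** Take the response as y = symptom-free positive-swab days, with d = positive-swab days and arm as the only covariate. The mean is d × exp(a + b × arm), and the estimate is

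exp(b) = (Σy/Σd in vaccine) / (Σy/Σd in placebo).

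This is q_V/q_P, the ratio of symptom-free shares among the infected. Neither the number at risk nor the number infected appears as a denominator.

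**Step 4: size.** The documents give no shares, so q is an assumption. The comparison uses time at risk and equal positive days per infection in both arms: rate ratio = (16 × q_V/110.3) / (28 × q_P/50.1) = 0.260 × q_V/q_P.

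| q vaccine / q placebo | 1 − ratio, 11.4 model | 1 − ratio, time at risk |
|---|---|---|
| equal | 0% | 74.0% |
| 0.7 / 0.5 | −40% | 63.7% |
| 0.9 / 0.5 | −80% | 53.3% |
| 0.5 / 0.7 | +28.6% | 81.5% |

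The first row is the clearest: with 16/628 against 28/302 infected, the 11.4 model returns no effect. These four pairs are illustrations, not limits. The mirror of the widest pair, 0.5/0.9, gives 1 − 0.556 = +44% against 1 − 0.260 × 0.556 = 86%.

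**The case against.** **The model fits its endpoint.** A Poisson count with offset log(positive days) is a standard model for the listed proportion, and that proportion is undefined without a positive swab. On this view, naming the full sets instead of the PCR-positive sets is a labelling slip. This stands in part: the mismatch is between objective and endpoint, and the protocol's endpoint list shares it. Switching to the PCR-positive sets would cure log(0) but leave the efficacy objective unanswered.

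**Infection prevention is estimated elsewhere.** Section 9.2 covers all infection and 10.1 covers A/VMS, both by Cox models, and section 12 lists models of infectious time averted. A reader might infer that the plan overlooks prevented infections altogether; it does not. Still, no section estimates efficacy against the composite with pre-symptomatic infection, and the section 12 item is high-level and not assigned to it.

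**The adjustment handles selection.** It refers to supporting analysis 2, which adjusts for baseline variables because the study is a post-randomization subset of the parent trial. It does not address conditioning on infection and cannot restore uninfected person-time.

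**Negative efficacy is an inference.** A reader might conclude that the plan will report negative VE, or that software will silently drop the uninfected. Section 11.4 does not say that VE is 1 minus the rate ratio, and a ratio above 1 could be reported simply as a higher symptom-free share. Handling of log(0) depends on the software. Both objections stand, as does the point that the sign depends wholly on the assumed shares.

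**Conclusion.** As written, section 11.4 yields either a failed fit or a symptom-free share ratio among the infected. Neither is efficacy against the composite. The offset is undefined for about 95% of the PAS and mITT sets up to crossover dose 2, and for somewhat fewer over full follow-up. Neither fault depends on that exact percentage.

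The divergence in size rests on assumed shares, on equal positive days per infection, and on reading 1 minus the ratio as efficacy. What needs no assumption about the level of the shares is that equal shares give a ratio of 1 whatever the efficacy against infection.

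The objective is exploratory. The documents do not support extending the point to the primary or secondary estimates, none of which uses this model.

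**What to change.** Estimate the objective in all PAS and mITT participants who have time at risk, by one of two routes, and state the response, the arm contrast and the censoring.

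1. **Time to first infection that is A/VMS or pre-symptomatic at detection**, by Cox model, censored as in section 9.2. This answers the objective most directly. It needs a written rule for classifying symptoms at detection from the parent-study data.
2. **Symptom-free PCR-positive swab days per participant**, by Poisson or negative binomial model with offset log(valid swabs tested or time at risk) and robust variance. Label it VE against symptom-free shedding burden, because it mixes prevention of infection with duration of shedding. It also leaves out very mildly symptomatic days, which the objective includes.

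Either route needs a stated rule for participants with no time at risk. Table S2 has 682 in the PAS and 930 in the mITT set, against 691 in Table S1 and 957 in Table S3, and the supplement does not explain the difference.

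Keep the present proportion as a descriptive summary by arm in the PCR-positive sets, without calling it VE. Section 3.1 defines PP-ITT, PP-PAS and PP-PAS2 but no PCR-positive mITT set.

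The cost is a revision of SAP 11.4 with matching endpoint wording in SAP 2.2 and protocol 3.3.3. It uses the swab and parent-study symptom data already planned.
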